### Sample size

Calculation of number of participants required for the clinical trial: for calculation of significant number of participants, the following is hypothesized based on the previous literature:Level of significance, α = 0.05;Type II error (β) is set at 0.2 with power of the test set at 80%;According to a previous clinical study using VAS as the main assessment tool for Chuna manual therapy in neck pain patients, the effect size of Chuna manual therapy in comparison to the control can be considered to be 1.03 [30], and 1.49 [31], respectively;Compliance rate will be set at 85% (the predicted rate of receiving ≥ 6 sessions of treatment during the five-week treatment period);For calculation of sample size, G*Power 3.1.7 was used. With evidence from item (3), application of mean ± SD resulted in conservatively hypothesizing the effect size of this clinical trial as 0.6 because of the high clinical heterogeneity of manual therapies such as Chuna. Application of items (1) and (2) and the effect size resulted in the calculation of a sample size of 90 participants (45 in each group).The mean comparison of pain requires a total of 90 participants (45 in each group), which is the minimum number of participants needed for testing the abovementioned hypothesis. Considering that 15% of participants received < 6 sessions of treatment within the five-week treatment period, a total of 108 participants, 54 in each group, will be extracted for the study.

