### Statistical analysis

The main evaluation method will be by intention-to-treat (ITT) analysis that evaluates participants who received at least one session of treatment. Per-protocol (PP) analysis will also be performed, which analyzes only participants who complete participation in the clinical trial in the initial allocated group, excluding participants who withdrew or crossed over during the study. Missing values will be processed mainly by multiple imputation, and last observation carried forward (LOCF) will be used for sensitivity analysis. Participants who received ≥ 6 sessions of treatment during the five-week treatment period will be analyzed separately.

The sociodemographic characteristics and treatment expectancy of participants will be evaluated by group. Continuous variables will be presented as average (standard deviation) or median values (quartile), and the two groups will be compared using Student’s t-test. Wilcoxon rank-sum test will be conducted if the data do not follow normal distribution. Categorical variables will be presented as frequency values (%), and Chi-square test or Fisher’s exact test will be performed as appropriate.

The efficacy variable for this clinical trial is the difference in continuous outcomes (i.e. NRS, VAS, NDI, NPQ, EQ-5D-5 L, SF-12) between baseline and predetermined timepoints. The primary endpoint is one week after completion of treatment (seven weeks after random allocation). Baseline values of each outcome and covariant factors which show statistical difference between groups at baseline will be set as covariates, and analysis of covariance (ANCOVA) with the treatment groups designated as the fixed factor. In addition, to examine the trend difference by visit, repeated measure (RM) ANCOVA will be performed.

To compare the total difference in outcome between the two groups within the treatment period (six weeks) and total study period (one year), the area under the curve (AUC) by specific timepoint after random allocation will be calculated and compared using the Student’s t-test.

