### Economic evaluation

Economic evaluation will be performed simultaneously with the clinical study to determine the cost-effectiveness of Chuna manual therapy and usual care. The primary economic outcome will be cost per quality-adjusted life years (QALY) gained. The primary economic endpoint will be  set for the study period and for the follow-up period; when estimation for time after this period is needed, it will be by extrapolation of cost and effect using a regression model or secondary analysis that performs decision modeling analysis. Treatment fees from the clinical trial will be calculated by combining the number of treatment sessions and unit fees, where the unit fee will be based on data from national health insurance and fees as charged at the study sites. Estimation of quality of life for calculation of QALYs will use quality of life estimates as deduced by EQ-5D-5 L as the evaluation variant; the AUC method will be used. When the time horizon exceeds 12 months, the fee unit will be standardized to 2017 Korean currency (Won) applying a 5% discount based on the economic evaluation guideline of HIRA. The analytic viewpoint of this study is from a social standpoint; representative values (mean) of the parameters used in the study will be used in baseline analysis. Sensitivity analysis will be performed through probabilistic sensitivity analysis using all possible estimated parameters and representative values.

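### The area-under-the-curve comparisons use an unadjusted t-test although the same section adjusts single-visit outcomes for baseline, so precision is given away and chance baseline gaps carry into the estimate

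*Protocol article*

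**What the plan says.** All references are to the protocol article.

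- **Statistical analysis, AUC paragraph.** To compare the arms over the treatment period, given there as six weeks, and over the full year, "the area under the curve (AUC) by specific timepoint after random allocation will be calculated and compared using the" Student's t-test. No covariate is named. The text does not say whether the AUC is built from the scores themselves or from changes from baseline.
- **Statistical analysis, preceding paragraph.** The efficacy variable is the difference between baseline and set timepoints. It is analysed by ANCOVA, with "Baseline values of each outcome" among the covariates and treatment group as the fixed factor. A repeated-measures ANCOVA is added for the trend by visit.
- **Economic evaluation.** QALYs come from EQ-5D-5L values, and "the AUC method will be used". No model for comparing QALYs between arms is named.
- **Randomization and allocation concealment.** Randomisation is stratified by site, with 54 participants per arm.
- **Length of treatment.** The Abstract, Trial design, Interventions and Sample size sections describe five weeks of treatment, and the Statistical analysis section itself also refers to a five-week treatment period.

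**The concern.** A participant's AUC is correlated with that participant's starting level. If it is an area under the scores, high starters tend to have high areas, and the baseline value is normally the first point of the area. If it is an area of change from baseline, high starters tend to show more change. In both cases part of the between-patient spread in the AUC can be predicted from a value the trial already holds. A two-sample t-test leaves that part in the error term. It also leaves in the point estimate whatever baseline difference chance has produced between the arms.

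The plan accepts this reasoning for outcomes at single timepoints and drops it, without giving a reason, for the summary over time. Because the test is named, this is a stated choice and not a detail left to another document. At stake is the precision of the comparisons that summarise the effect over the treatment period and the year.

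**Working it through.** **1. The plan's own figure.** Inputs from Sample size: "Level of significance, α = 0.05"; "Type II error (β) is set at 0.2 with power of the test set at 80"%; "conservatively hypothesizing the effect size of this clinical trial as 0.6". A two-sided two-sample t-test with d = 0.6, by the noncentral t distribution with noncentrality d × √(n/2), gives power 0.795 at 44 per arm and 0.804 at 45. So 45 per arm (90 in total) reproduces: "The mean comparison of pain requires a total of 90 participants (45 in each group"). Allowing for 15%, 45/(1 − 0.15) = 52.9, or 53 per arm, against the stated 54. This calculation concerns the mean comparison of pain, not the AUC, so nothing below changes it.

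**2. Chance baseline gap.** With 54 per arm, the SD of the baseline difference between arms is √(2/54) = 0.192 baseline SDs, and its 95% range is ±1.96 × 0.192 = ±0.38.

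**3. Variance removed by adjustment.** Let r be the within-arm correlation between baseline and AUC. The documents give no value, so r = 0.3 to 0.6 is an assumption. The ratio of ANCOVA variance to t-test variance is 1 − r². Power uses 54 per arm, two-sided 0.05 and noncentrality [0.5/√(1 − r²)] × √(54/2), where 0.5 SD of the AUC is an illustrative effect.

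| r | 1 − r² | 1/(1 − r²) | Power for 0.5 SD |
|---|---|---|---|
| 0 (t-test) | 1.00 | 1.00 | 0.731 |
| 0.3 | 0.91 | 1.10 | 0.770 |
| 0.4 | 0.84 | 1.19 | 0.802 |
| 0.5 | 0.75 | 1.33 | 0.844 |
| 0.6 | 0.64 | 1.56 | 0.896 |

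Adjustment is therefore worth what 10% to 56% more participants would bring to the t-test.

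**4. Carry-over of the gap.** A baseline gap of g baseline SDs moves the unadjusted AUC difference by r × g SDs of the AUC. A gap of one SD (0.192) gives 0.3 × 0.192 = 0.06 to 0.6 × 0.192 = 0.12 SD of the AUC.

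**5. Is the assumed range too generous?** Take the one-year assessments at 0, 5, 13, 26, 39 and 52 weeks (baseline, five weeks, then 3, 6, 9 and 12 months), trapezoid weights, equal variances and a common between-visit correlation ρ, again assumed. The baseline weight is 2.5/52 = 0.048.

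| ρ | r for the one-year AUC | 1 − r² |
|---|---|---|
| 0.3 | 0.50 | 0.75 |
| 0.5 | 0.68 | 0.54 |
| 0.7 | 0.82 | 0.33 |

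Under this model r lies in the upper part of the 0.3 to 0.6 range or beyond it, so step 3 is cautious.

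**6. If the AUC is of change from baseline.** With V the variance of the AUC of scores and c its covariance with baseline (baseline variance 1), the ratio of ANCOVA variance to t-test variance is (V − c²)/(V + 1 − 2c).

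- ρ = 0.3: V = 0.440, c = 0.334, ratio 0.328/0.772 = 0.43.
- ρ = 0.5: V = 0.600, c = 0.524, ratio 0.325/0.552 = 0.59.
- ρ = 0.7: V = 0.760, c = 0.714, ratio 0.249/0.331 = 0.75.

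Precision is lost here too. The chance gap then acts in the opposite direction, because c − 1 is negative.

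**The case against.** The strongest defence is that the t-test is a legitimate analysis of a randomised comparison. It is unbiased on average, keeps its type I error, and its standard error already allows for chance imbalance. That stands. A reader might infer that the AUC results would be biased or invalid; they would not. What is lost is precision, and accuracy given the baseline difference that actually occurs.

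Second, the AUC is not the trial's only long-term answer on pain. Baseline-adjusted ANCOVA at set timepoints, with follow-up to 12 months, and repeated-measures ANCOVA are also planned. This stands too and limits the importance of the point.

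Third, at the trial's planning effect of 0.6, the unadjusted t-test with 54 per arm already has power 0.871. But that effect was assumed for the VAS comparison, and no effect is stated for the AUC.

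Fourth, a reader might infer that QALYs will be compared without baseline adjustment. The article does not support this. The AUC method is how a QALY is computed, not how arms are compared; the text names no comparison model and rules out no adjustment, and a condensed article may leave this to a fuller document. Nor can one say that a chance utility gap would rival the QALY difference, since no expected QALY difference is given.

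None of this supplies a reason to prefer the t-test for the AUC.

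**Conclusion.** The point holds for the AUC comparisons. The article fixes an unadjusted t-test where its own approach to the same outcomes is baseline-adjusted, and this is the less precise choice. With an assumed baseline-AUC correlation of 0.3 to 0.6, 9% to 36% of the variance is left in unnecessarily, and power for a 0.5 SD effect is 0.73 where 0.77 to 0.90 was available. The direction does not depend on whether scores or changes are summed; the size depends on correlations that the documents do not give. This is an improvement to a supplementary analysis, not a threat to the trial's main conclusion.

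On QALYs the conclusion is a recommendation, not an error. Separately, the six-week treatment period in the AUC paragraph conflicts with the five weeks given elsewhere, so the window of the treatment-period AUC is not defined until these passages are reconciled.

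**What to change.** - Replace Student's t-test for each AUC by ANCOVA on arm, the baseline value of that outcome, and site, which is the randomisation stratum. State whether the AUC is built from scores or from changes; with baseline as a covariate and the same visits and window, the estimated arm difference is the same either way.
- Reconcile the six-week and five-week statements, and name the start, end and visits of the treatment-period AUC.
- As a secondary recommendation, state that the QALY difference is estimated by regression on arm, baseline EQ-5D-5L utility and site, and carry that estimate into the base case and the probabilistic sensitivity analysis.

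The cost is wording only. The planned ANCOVA and the QALY calculation already need the baseline values, site is recorded for randomisation, and the sample size does not change. The change should be made before unblinded data are seen.

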**Methods/Design:**

This study is the protocol for a two-armed parallel, assessor-blinded, multicenter, randomized controlled trial. A total 108 patients with chronic neck pain (time to onset ≥ 3 months, numeric rating scale [NRS] of neck pain ≥ 5) will be recruited at five Korean medicine hospital sites. Participants will be allotted to one of two groups (*n* = 54, respectively): the Chuna manual therapy group, and the usual care (conventional physical therapy and medication treatment) group. Ten sessions of Chuna manual therapy or usual care will be administered twice a week for five weeks. Since the study design does not permit patient or physician blinding, the outcome assessor and statistician will be blinded. The primary outcome will be the visual analogue scale (VAS) of neck pain at 5 weeks after randomization. Secondary outcomes include the VAS of radiating arm pain, NRS of neck pain and radiating arm pain, Vernon-Mior neck disability index (NDI), Northwick Park neck pain questionnaire (NPQ), EuroQol-5 Dimension (EQ-5D), EQ-VAS, patient global impression of change (PGIC), economic evaluation, adverse effects, and drug consumption. Follow-up outcome assessments will be conducted at 3, 6, 9, and 12 months after randomization.

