**Fig. 2 Fig2:**
[figure not shown]
Timepoints of each assessment index

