Specific timepoints where the VAS and NRS fall under the half line point of the baseline standard will be performed for a comparative analysis on patient improvement rate. To measure the time between random allocation to the point when neck pain improves to less than half the original pain intensity, Kaplan–Meier survival analysis will be used for analysis and the curve will be compared using the log-rank test. A Cox model will be used to calculate the hazard ratio to compare the speed at which pain improves to less than half the original pain. Whether the recovery speed differs by subgroup will also be examined.

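### Time to a 50% pain reduction is known only to the interval between assessments, but Kaplan–Meier and Cox treat it as exact; depending on tie handling the hazard ratio can shrink toward 1, and medians are read late

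*Protocol article*

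**What the plan says.** The Statistical analysis section reads the event from repeated pain scores: "Specific timepoints where the VAS and NRS fall under the half line point of the baseline standard". The stated purpose is "To measure the time between random allocation to the point when neck pain improves to less than half the original pain intensity". For this, Kaplan–Meier "survival analysis will be used for analysis and the curve will be compared using the log-rank test", and then "A Cox model will be used to calculate the hazard ratio to compare the speed at which pain improves". Differences in recovery speed between subgroups are to be examined as well.

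On when pain is scored, the Abstract says "The primary outcome will be the visual analogue scale (VAS) of neck pain at 5 weeks after randomization" and "Follow-up outcome assessments will be conducted at 3, 6, 9, and 12 months after randomization". Treatment visits are more frequent: "Ten sessions of Chuna manual therapy or usual care will be administered twice a week for five weeks". The full schedule is in Fig. 2, titled "Timepoints of each assessment index", and that figure is not available here.

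The article names no method for tied event times and no interval-censored or discrete-time model. Time to halving of pain is not the primary outcome and is not among the listed secondary outcomes. The primary analysis is an ANCOVA of the change in VAS.

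**The concern.** A participant who is above half of baseline at one assessment and below it at the next crossed somewhere in between. Entering the later visit date as the event time does two things. It moves every event to the end of its interval, so the Kaplan–Meier curve drops only at visits and the median is read at a visit. It also creates ties, which the Cox partial likelihood handles only approximately unless an exact method is used.

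The hazard ratio is the article's chosen measure of recovery speed. At stake is a published figure that may understate a real difference, and a median presented as exact when it is known only to within several weeks or months.

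**Working it through.** **Plan's own figures.** The article gives no number for this analysis. Its sample size supplies the arm size: a two-sided t-test with effect size 0.6, α = 0.05 and 80% power needs 44.6, so 45 per arm and 90 in total. Then 90/0.85 = 105.9, or 106, against the stated 108. I used the stated 54 per arm.

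**Gaps between assessments.** Months 3, 6, 9 and 12 are about weeks 13, 26, 39 and 52. The gaps are 13 − 5 = 8 weeks, then 13 weeks each. Week 5 follows the Abstract and the Primary outcome section. Other parts of the article put the primary endpoint at week 6 or week 7, which would shorten the first gap to 7 or 6 weeks.

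**Why the tie method matters.** Take one interval in which proportions p0 (control) and p1 (treated) have the event. With all events tied at one time, the Breslow estimate solves to p1/p0, a ratio of proportions. The complementary log-log estimate is ln(1 − p1)/ln(1 − p0), the hazard ratio itself. Under proportional hazards with a true ratio of 2, p1 = 1 − (1 − p0)².

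- p0 = 0.30 (assumed): p1 = 1 − 0.49 = 0.51. Breslow gives 0.51/0.30 = 1.70; complementary log-log gives 2.0.
- p0 = 0.40 (assumed): p1 = 1 − 0.36 = 0.64. Breslow gives 0.64/0.40 = 1.60; complementary log-log gives 2.0.

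**Simulation over the whole year.** Exponential times, 54 per arm, follow-up to week 52, control medians of 4, 8 and 20 weeks, each event dated at the next assessment. There were 200 runs per case (60 for complementary log-log), and the table shows the range of median estimates over the three control medians. Event rates, hazard ratios and schedules are all assumptions. Each schedule ends with weeks 13, 26, 39 and 52.

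| True HR | Scoring to week 5 | Breslow | Efron |
|---|---|---|---|
| 1.5 | twice weekly | 1.36–1.41 | 1.46–1.52 |
| 1.5 | weekly | 1.32–1.39 | 1.42–1.49 |
| 1.5 | week 5 only | 1.24–1.38 | 1.45–1.47 |
| 2.0 | twice weekly | 1.68–1.78 | 1.89–2.00 |
| 2.0 | weekly | 1.65–1.75 | 1.87–1.97 |
| 2.0 | week 5 only | 1.36–1.77 | 1.76–2.03 |

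Over all schedules the complementary log-log model gives 1.50–1.59 for a true 1.5 and 1.94–2.06 for a true 2.0. At a true 1.0 every method gives 0.95–1.06. A separate simulation with control medians of 6.8–9.7 weeks gives, for a true 2.0, 1.50–1.70 (Breslow), 1.85–1.97 (Efron) and 2.01–2.10 (complementary log-log).

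**Medians.** If 30% of controls respond by week 5, the exponential median is 5 × ln 2/(−ln 0.70) = 9.7 weeks; if 40%, it is 5 × ln 2/(−ln 0.60) = 6.8 weeks. Both are read at week 13, so 13 − 9.7 = 3.3 to 13 − 6.8 = 6.2 weeks late. In the simulation a true control median of 8 weeks is read at about 13 and one of 20 at about 27, so about 5 and 7 weeks late. A true 4 weeks reads 4.9–6.1. Treated medians of 2.0–2.7 weeks are only 0.2–0.5 weeks late with weekly or twice-weekly scoring, but are read at week 5 if that is the first assessment. No tie option changes any of this.

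**The case against.** The strongest reply is that the loss comes from a tie option and not from the Cox model. Efron ties leave a true 1.5 at 1.42–1.52 and a true 2.0 mostly at 1.85 or above; the lowest value, 1.76, needs the sparsest schedule and a fast response. The article does not choose Breslow. Naming SAS 9.4 does not settle it, since the documents say nothing of that software's defaults. A tie option is also the kind of detail an article leaves to an analysis plan. This stands: a reader might infer that the hazard ratio is necessarily biased toward 1, and the documents do not support that.

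A reader might also infer that the event is seen at only a handful of visits. That is not established either. Fig. 2 is not shown, the Blinding section has the assessor evaluating participants before treatment, and the plan includes a by-visit trend analysis and an area under the curve for the treatment period. These suggest scoring in weeks 1–5 without proving it. Frequent early scoring does not remove the Breslow loss (a true 2.0 still reads 1.68–1.78 with twice-weekly scoring), and it leaves the long gaps after week 5 as they are.

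The first sentence of the plan on this endpoint may already intend response rates by timepoint, which would show the grouped nature of the data. Its wording is too unclear to be sure.

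The part that no tie option or unseen schedule answers is narrower: the article commits to methods for exact times, the event is interval-censored, and medians that fall after week 5 are read late.

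**Conclusion.** The point holds as a low-severity improvement to a supportive analysis. For a true hazard ratio of 2.0, the Cox estimate may be 11–32% low with Breslow ties (1.78 to 1.36) and at most 12% low with Efron ties (1.76), while a grouped-time model recovers it on every schedule tried. Control-arm medians after week 5 are about 3–7 weeks late in the cases worked. Thirteen weeks is the upper bound from the longest gap, not an expected delay.

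These sizes rest on assumed exponential times, event rates, hazard ratios and schedules, because the article gives none for this endpoint. The simulations covered the overall comparison only, so they say nothing on the size of any effect on subgroup hazard ratios. Nor should the point be read as a threat to the trial's main conclusion. With a common assessment schedule the log-rank test keeps its validity under the null, all methods centre near 1.0 when there is no effect, and the VAS comparison does not use this endpoint.

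**What to change.** Replace the sentence on the Cox model with one to this effect: *Time to the first assessment with pain below half of baseline will be treated as interval-censored; the hazard ratio will be estimated with a discrete-time proportional-hazards model (complementary log-log link, assessment as the time factor) or an interval-censored proportional-hazards model, and each median will be reported as the interval between the two assessments that contain it.* Showing the proportion of responders at each assessment beside it would help the reader.

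If the Cox model is kept, name exact or Efron ties. The log-rank comparison can stay. The cost is a sentence of text and a slightly less familiar model to explain; no new data, visits or change to the primary analysis are needed.
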